### Data collection

Demographic data, including age, sex, American Society of Anesthesiologists classification, body mass index, underlying diseases, type and duration of the surgical procedure, and type of surgical procedure, will be collected upon inclusion in the study. Postoperative medications including opioids and other analgesics will also be collected.

All postoperative monitoring variables measured by the nurses (HR, RR, SpO2, SAP, DAP, and temperature) during the first 72 postoperative hours at a frequency determined by the medical indications will be collected using Easily software and recorded on a dedicated electronic case report form (eCRF). The time of occurrence of any complications noted by nurses and doctors will also be recorded on the eCRF.

The wearable device transmits the measurement data every 5 minutes to the Biobeat Gateway through Bluetooth. All data are uploaded to and stored on the
Instamed (a French telemedicine company and Biobeat’s partner) certified health data hosting cloud (hosted by Amazon Web Services and General Data Protection Regulation compliant). The research team can then access data through the Instamed platform as well as request that data be exported as.csv files. Nursing staff and doctors will not have access to monitoring data during the protocol duration. The data will be deleted at the end of the study and can be deleted during the study as needed.

### Outcome measures

The main outcome is the occurrence of one or more episodes with a mean arterial pressure below the threshold of 60 mmHg during the first 72 hours following a major non-cardiac surgical procedure unless death or hospital discharge occurs sooner, with the 72-hour period starting when the patient returns to the surgical department. The secondary outcomes will concern the frequency of postoperative respiratory or temperature abnormalities and their duration, the frequency of artefacts and blank/null outputs from the wearable device and, more globally, the signal-level validity, the postoperative complications that occurred during the monitoring period, as determined by the healthcare team in accordance with the Dindo and Clavien classification
^
12
^ and the comprehensive complication index.
^
13
^ Finally, the ease of use of the device at the time of insertion and the patient’s tolerance to wearing the Biobeat
^®^ device will also be determined. Definitions of hemodynamic, respiratory, and temperature abnormalities are listed in
Table 1.

**Table 1. T1:** Outcome definitions.

Primary Outcome Measure
Postoperative haemodynamic abnormality
• a MAP < 70 mmHg
• or a MAP < 65 mmHg
• or a MAP < 60 mmHg
• or a MAP < 80% of the value measured during the pre-anaesthesia consultation
• or a MAP < 70% of the value measured during the pre-anaesthesia consultation
• or a MAP < 80% of the value measured in the OR before the induction of anaesthesia
• or a MAP < 70% of the MAP measured in the OR before the induction of anaesthesia
• or a MAP > 100 mmHg
• or a MAP > 110 mmHg
• or a MAP > 120 mmHg
• or a MAP > 130 mmHg
• or a MAP > 120% of the MAP measured during the pre-anaesthesia consultation
• or a MAP > 130% of the MAP measured during the pre-anaesthesia consultation
• or a MAP > 120% of the MAP measured in the OR before induction of anaesthesia
• or a MAP > 130% of the MAP measured in the OR before induction of anaesthesia
• or a heart rate < 40/min
• or a heart rate > 100/min
• or a rhythm disorder
Secondary Outcomes
Postoperative respiratory abnormality
• breathing rate < 8/min
• breathing rate > 20/min
• or a peripheral oxygen saturation < 95%
• or a peripheral oxygen saturation ≤ 92%
• or a peripheral oxygen saturation ≤ 90%
• or a peripheral oxygen saturation ≤ 85%
Postoperative temperature abnormality
• a temperature ≤ 36.8°C
• or a temperature ≥ 38°C
• or a temperature ≥ 39°C

MAP: mean arterial pressure; OR.

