## Abstract

**Background**: Postoperative hypotension associated with postoperative morbidity and early mortality has been studied previously. Hypertension and other hemodynamic, respiratory, and temperature abnormalities have comparatively understudied during the first postoperative days.

**Methods**: This bi-centre observational cohort study will include 114 adult patients undergoing non-cardiac surgery hospitalized on an unmonitored general care floor and wearing a multi-signal wearable sensor, allowing remote monitoring (
Biobeat Technologies Ltd, Petah Tikva, Israel). The study will cover the first 72 hours after discharge of the patient from the post-anaesthesia care unit. Several thresholds will be used for each variable
(arterial pressure, heart rate, respiratory rate, oxygen saturation, and skin temperature). Data obtained using the sensor will be compared to data obtained during the routine nurse follow-up. The primary outcome is hemodynamic abnormality. The secondary outcomes are postoperative respiratory and temperature abnormalities, artefacts and blank/null outputs from the wearable device, postoperative complications, and finally, the ease of use of the device. We hypothesize that remote monitoring will detect abnormalities in vital signs more often or more quickly than the detection by nurses’ routine surveillance.

**Discussion**: A demonstration of the ability of wireless sensors to outperform standard monitoring techniques paves the way for the creation of a loop which includes this monitoring mode, the automated creation of alerts, and the sending of these alerts to caregivers.

**Trial registration**: ClinicalTrials.gov,
NCT04585178. Registered on October 14, 2020

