### Statistics

Sample size

Our main goal is to estimate the proportion of patients showing severe hypotension and, notably, to corroborate the prevalence found in Liem
*et al.*
^
5
^
*i.e.*, 8%. To gain a 10% precision (± 5%) with a two-sided 5% alpha risk, 114 patients need to be included.

Detection of artefacts

This will follow similar rules as previously published in a paper dedicated to the validation a new sensor.
^
14
^ The rules selected to define artefacts may be updated according to experience and the literature.
^
15
^ The successive rules will be recorded in a register, and all recordings will be reviewed in the light of these new rules.

Missing values

Missing data will not be replaced.

Statistical analyses

Descriptive summaries will be provided for each parameter and for each device. For continuous variables, the mean, median, and their 95% confidence limits, obtained using bootstrapping methods, will be provided. For discrete variables, counts, percentages, and confidence limits obtained using a bootstrap method will be provided
*.*

The proportion of data gaps and artefacts for each parameter will be given as a percentage of the total number of measurement points and observations, respectively, with the corresponding 95% confidence interval (CI).

When physiologic parameters (HR, SAP, DAP, for instance) are measured simultaneously by nurses and wearable devices, a Bland-Altman analysis for repeated measurements, accounting for multiple observations per individual, will be performed to draw mean-difference plots and derive accuracy or bias (mean difference), precision (standard deviation of difference), and limits of agreement (LoAs) that are expected to contain 95% of the paired differences between measurements by the nurses and the wireless patch, with their confidence intervals.

At the patient level and for each kind of clinical event, the proportion of patients with detection of at least one event (hypotension, for instance) by a nurse and wearable monitoring will be described in a two-by-two table. Agreement will be estimated by Cohen’s kappa coefficient with its 95% CI, while differences will be tested by a non-parametric McNemar test for paired nominal data.

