The time (hours) to first occurrence of data loss or end of service of the device, or to the first occurrence of a clinical complication, will be described with Kaplan-Meier survival curves, and, if permitted by the number of such events, risk factors will be explored by a Cox model.

Interim analyses are not planned in this study.

A two-tailed p value < 0.05 will be considered statistically significant. All statistical analyses will be performed using R software (R Development Core Team, 2012.
https://www.r-project.org/).

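### The primary outcome is stated in two ways: MAP below 60 mmHg in the outcome text, any of 18 haemodynamic criteria in Table 1; the sample size fits only the first

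*Protocol article*

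**What the plan says.** The article describes the primary outcome in four places.

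- **Outcome measures, text:** "The main outcome is the occurrence of one or more episodes with a mean arterial pressure below the threshold of 60 mmHg", over the 72 hours after return to the surgical department (less if the patient dies or is discharged earlier).
- **Table 1, primary-outcome block:** postoperative haemodynamic abnormality, as a list joined by 'or'. It opens with MAP below 70 mmHg, continues with "or a MAP < 65 mmHg" and other low-pressure rows, moves to high-pressure rows such as "or a MAP > 100 mmHg", and closes with two heart-rate rows and "or a rhythm disorder".
- **Abstract:** "The primary outcome is hemodynamic abnormality", with no threshold.
- **Statistics, Sample size:** "Our main goal is to estimate the proportion of patients showing severe hypotension", with an expected 8%, a precision of ± 5 points and 114 patients.

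The outcome text refers to the table for definitions ("Definitions of hemodynamic, respiratory, and temperature abnormalities are listed in" Table 1) but does not say how the list relates to the single criterion it has just given. Its secondary outcomes cover respiratory and temperature abnormalities, signal quality, complications, ease of use and tolerance. The remaining haemodynamic thresholds are not among them. The Statistics section plans a two-by-two table, kappa and a McNemar test for each kind of clinical event, and adds "A two-tailed p value < 0.05 will be considered statistically significant".

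**The concern.** A trial report leads with its primary outcome. Here the outcome text and the sample size point to one low-pressure criterion, while Table 1 and the abstract point to a broad category that also includes high pressure, heart rate and rhythm. The two definitions give different headline proportions, and the planned precision belongs to only one of them. Since the other haemodynamic thresholds are not listed as secondary outcomes, the primary heading is the only place they appear. An author could report any one of them, or their union, as the primary result and cite the protocol in support.

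**Working it through.** **1. The plan's own figure.** Inputs from Statistics, Sample size: p = 0.08, half-width d = 0.05, two-sided alpha 0.05 (z = 1.960).

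n = z² p(1 − p) / d² = 3.8415 × 0.08 × 0.92 / 0.0025 = 113.09, rounded up to **114**. The stated number reproduces. Reading the precision as ± 10 points gives 28.3, and a one-sided alpha gives 79.7, so only the two-sided ± 5 version matches. At N = 114 the half-width is 1.960 × √(0.0736/114) = ± 4.98 points.

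**2. Which outcome this serves.** The 8% is an expected prevalence of severe hypotension. The sample-size paragraph does not repeat the 60 mmHg cut-off, but MAP below 60 mmHg is the lowest absolute threshold in Table 1 and the criterion in the outcome text. The Limitations section also ties the number of patients to postoperative hypotension. No prevalence is given for the Table 1 category or for any other threshold.

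**3. Count of the Table 1 primary rows.** 7 low-MAP + 8 high-MAP + 2 heart-rate + 1 rhythm = **18**.

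**4. Table 1 read as one composite.** Under 'or', a stricter threshold adds nothing to a looser one on the same scale:

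| Retained row | Rows it makes redundant | Number |
|---|---|---|
| MAP < 70 mmHg | < 65, < 60 | 2 |
| < 80% of consultation value | < 70% of it | 1 |
| < 80% of pre-induction value | < 70% of it | 1 |
| MAP > 100 mmHg | > 110, > 120, > 130 | 3 |
| > 120% of consultation value | > 130% of it | 1 |
| > 120% of pre-induction value | > 130% of it | 1 |

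The total is **9 redundant rows of 18**, and MAP below 60 mmHg is one of them.

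Half-width at N = 114, 1.960 × √(p(1 − p)/114), over an *assumed* range for the composite's prevalence:

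| Prevalence (assumed) | Half-width, points | N needed for ± 5 |
|---|---|---|
| 20% | 7.3 | 246 |
| 50% | 9.2 | 385 |
| 80% | 7.3 | 246 |
| 90% | 5.5 | 139 |
| 92% | 5.0 | 114 |
| 95% | 4.0 | 73 |

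The formula is symmetric about 50%, so ± 5 points holds only at or below about 8%, or at or above about 92%.

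**5. Table 1 read as a menu.** Each threshold is then analysed by itself, which fits the abstract's remark that several thresholds will be used per variable. This removes the composite, but up to 18 results remain under the primary heading, and no section ranks them.

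**The case against.** The strongest reply is that the intention is clear enough. The outcome text, the stated main goal and the sample size all agree on low pressure; only a table heading and one sentence of the abstract differ. Table 1 is a table of definitions, and nested cut-offs make sense as a menu but not in a composite. The main goal is estimation, and an analysis plan that is not shown could settle the order of analyses.

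Much of this stands. The menu reading is at least as plausible as the composite, MAP below 60 mmHg is very probably what was meant, and the sample size is not wrong. The contradiction remains all the same. Both versions are printed in full, so condensation for a journal does not explain it, and a later plan that adopted one would contradict the other. The menu reading itself leaves the rows unranked.

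Three stronger inferences are tempting, and the document supports none of them:

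- **That the composite would be positive in nearly every patient.** A reading every 5 minutes gives up to 72 × 60/5 = 864 readings, so a high sensor prevalence is plausible. But for 95% of patients to be positive, the share of qualifying readings would have to be 0.35% with 864 independent readings, 4.1% with 72 effective readings and 39.3% with 6. The article gives neither that share nor the correlation between readings, and nurses' spot checks need not behave like the sensor.
- **That a near-universal outcome could not separate the two methods.** McNemar's test depends on discordant pairs. If, hypothetically, the sensor flagged 100% and the nurses 93% of 114 patients, about 8 pairs would be discordant, all in one direction, and the exact p-value would be 2 × 0.5⁸ = 0.008.
- **That a particular false-positive rate follows.** The example given of a kind of clinical event is hypotension, not each cut-off. The number of tests is therefore not fixed, and nested thresholds are strongly correlated.

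**Conclusion.** The inconsistency is real and can be seen by comparing the outcome text with Table 1 and the abstract. N = 114 supports only the hypotension outcome. Under the composite reading, half the rows are redundant, the criterion behind the sample size loses its separate role, and the planned precision fails at any prevalence between about 8% and 92%, by up to 4.2 points (9.2 against 5). How far it would fail in practice is unknown: the composite's prevalence is not given, and that it could be high is an assumption. Under the menu reading there is no precision problem for MAP below 60 mmHg itself, but the headline threshold stays open to choice after the data are seen. Under either reading of Table 1, the document does not fix a single primary result. The conclusion takes severe hypotension in the sample-size paragraph to mean MAP below 60 mmHg, as the outcome text implies.

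**What to change.** Name one primary outcome in the same words in the abstract, the outcome text and Table 1: at least one episode of MAP below 60 mmHg within 72 hours. State in the sample-size paragraph that severe hypotension means this criterion. Move the other Table 1 haemodynamic rows to the secondary outcomes, each reported separately with a 95% CI and treated as exploratory, and say that they are not combined into one composite.

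The change is to wording only. N stays at 114 and no extra patients or measurements are needed. The Methods section requires modifications to go to the ethics committee, and the registry entry, which was not available for this review, should be checked for agreement. Recruitment was described as ongoing, so the change should be made and dated before the data are analysed. The real cost is that the other thresholds, including all the hypertension rows, lose primary status.

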### The studied device

Patients will be equipped with a portable Biobeat
^®^ sensor, a single-use patient device that consists of a skin patch placed 1 cm to the left of the sternum, just below the clavicle (
Biobeat Technologies Ltd, Petah Tikva, Israel) (
Figure 1). The sensor continuously records the photoplethysmographic waveform, which allows recording and calculation of several physiological parameters: heart rate (HR), respiratory rate (RR), peripheral oxygen saturation (SpO
_2_), systolic arterial pressure (SAP) and SAP variation, diastolic arterial pressure (DAP) and DAP variation, and skin temperature. Other variables, stroke volume and cardiac output, are measured by this sensor but are not included in this protocol.

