**Figure 1. f1:**
[figure not shown]
The sensor and placement of the patch sensor (consent obtained for publication).

Biobeat
^®^ is CE approved (N°688840; March 19, 2019), and its use was also approved by the FDA in 2019 (510K clearance for measurement of arterial pressure, oxygenation and HR in hospitals, clinics, and long-term care and at home).

High agreement has been demonstrated for arterial pressure measurements obtained via the Biobeat
^®^ sensor and the gold-standard sphygmomanometer technique.
^
10
^

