### Limitations

Our protocol suffers from several weaknesses. The first is that this study will take place during the COVID-19 pandemic, which profoundly changes hospital activity and its functioning. In addition, patients included in the study are at intermediate risk since their procedure will last more than 2 hours and they are expected to have a postoperative stay of more than 72 hours but are not expected to be hospitalized in a monitored unit. This obviously reflects a practice specific to each health facility. We decided not to include in the study patients with very hairy thoracic skin since we decided not to ask patients to shave their chests. This induces a bias in the selection of the patients due to the non-inclusion of some men. We chose to have data registered by the nurses gathered at a frequency determined by medical indications and not by a priori determined intervals. Such choice could be considered as a weakness of the protocol, but we wanted to do a real-life study and consequently to have instructions given to nurses by the medical team which may vary from one patient to another. It is of prime importance to notice that only blood pressure measurement passed validation testing for accuracy
^
10
^ and not the other parameters measured by the Biobeat
^®^ sensor to the best of our knowledge. Although this may be a limitation to this study, we decided to use this device because it received approval from the Food and Drug Administration and European Community regulators. Finally, the number of subjects to be included in the study was based on the results of a previous publication on the occurrence of postoperative hypotension.
^
5
^ There is probably some difference between our population and our nursing monitoring modalities and the corresponding elements of this study.
^
5
^ We probably should have done a prior study to better specify the percentage of patients who had a postoperative hypotension in our center. In any case, including 114 patients will allow us to give a first answer to the interest of remote monitoring.

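### One site-free set of temperature cut-offs serves both a chest skin patch and the nurses' temperature, so the paired event comparison for temperature cannot be interpreted

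*Protocol article*

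**What the plan says.** The studied device section describes "a skin patch placed 1 cm to the left of the sternum, just below the clavicle". Its outputs include "diastolic arterial pressure (DAP) and DAP variation, and skin temperature". The Abstract says that several thresholds will be used for each variable and lists the variables as "arterial pressure, heart rate, respiratory rate, oxygen saturation, and skin temperature", so the cut-offs are meant to apply to the skin reading.

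Outcome measures names as a secondary outcome "the frequency of postoperative respiratory or temperature abnormalities and their duration". Table 1 then gives a single list: "a temperature ≤ 36.8°C", "or a temperature ≥ 38°C", and a third item at 39°C and above. It states no site, no minimum duration and no separate rule for patch and nurse.

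Data collection says that nurses record temperature among their routine variables, at a frequency set by medical indication and with no site or method given. It also says that the patch transmits every 5 minutes. Under Statistics, each kind of clinical event is reduced to whether a patient had one or more, by nurse and by patch. The resulting two-by-two table is analysed with Cohen's kappa and McNemar's test.

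**The concern.** A paired event table compares two detection methods only if both apply the same definition to the same quantity. Here the definition is shared, but the article calls one quantity skin temperature and the other simply temperature. It mentions no conversion between them and does not acknowledge a difference.

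If skin reads lower than what the nurses measure, the low cut-off is crossed more easily by the patch and the high cut-offs less easily, whatever the patient's state. The study hypothesis is that the sensor detects abnormalities more often. A significant McNemar result at the low cut-off would therefore read as confirmation when it may reflect only site and cut-off. The low cut-off adds a second difficulty: if typical ward temperatures lie close to 36.8°C, crossing it is ordinary fluctuation even on the nurse side, which sits badly with the label of abnormality.

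**Working it through.** **The plan's own figure.** The only stated sample-size figure is N = 114. With p = 0.08 and d = 0.05, n = 1.96² × 0.08 × 0.92 / 0.05² = 113.1, rounded up to 114. It reproduces and does not depend on temperature.

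**Inputs from the document.** 72 h at one reading per 5 min gives 72 × 60 / 5 = 864 patch readings. One qualifying reading makes a patient positive.

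**Inputs assumed.** Body mean 36.8-37.5°C; between- and within-patient SD 0.3°C each; correlation 0.95 between successive readings; skin lower than body by 0, 0.5 or 1°C; 9 or 18 nurse checks in 72 h, taken at body temperature. Each scenario simulated 4,000 patients. Nurse columns are from the no-offset run.

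Patients with one or more readings at or below 36.8°C:

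| Body mean | Patch, offset 0 | Patch, 0.5°C | Patch, 1°C | Nurses, 9 / 18 checks |
|---|---|---|---|---|
| 36.8 | 99% | 100% | 100% | 90% / 95% |
| 37.0 | 97% | 99.9% | 100% | 74% / 83% |
| 37.2 | 90% | 99.8% | 100% | 56% / 67% |
| 37.5 | 64% | 97% | 100% | 23% / 31% |

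Patients with one or more readings at or above 38°C:

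| Body mean | Patch, offset 0 | Patch, 0.5°C | Patch, 1°C | Nurses, 9 / 18 checks |
|---|---|---|---|---|
| 36.8 | 13% | 0.5% | 0% | 1.6% / 2.8% |
| 37.0 | 30% | 2.7% | 0.03% | 6% / 10% |
| 37.2 | 51% | 8.5% | 0.3% | 14% / 22% |
| 37.5 | 84% | 30% | 2.5% | 44% / 55% |

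With no offset, the patch exceeds the nurses at both cut-offs through denser sampling, which is the effect the study wants to see. An offset of 0.5°C is enough to reverse the order at 38°C.

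**Nurse side, second model.** Assume total SD 0.4°C with half the variance between patients, so each component has SD 0.4 × √0.5 = 0.283, and 9 readings. The share of single readings at or below 36.8°C is Φ((36.8 − mean)/0.4). The share of patients is 1 − E[(1 − Φ((36.8 − mean − b)/0.283))⁹], with b the patient effect.

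- Mean 36.9°C: 40% of readings, 83% of patients.
- Mean 37.2°C: 16% of readings, 52% of patients.
- Mean 37.5°C: 4% of readings, 20% of patients.

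**Effect on the paired analysis.** Suppose all 114 patients are patch-positive and the nurses flag a of them. Observed agreement is a/114. Expected agreement is (114/114) × (a/114) + 0 = a/114. Kappa is therefore 0 whenever a < 114. All discordant patients favour the patch, so the exact McNemar p is 2 × 0.5^(114 − a):

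- Nurses flag 108 (95%), 6 discordant: p = 0.031.
- Nurses flag 103 (90%), 11 discordant: p = 0.001.

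**The case against.** The strongest reply is that the sizes come from outside the document. It gives no temperature distribution, no skin-to-body offset, no nurse site, and no statement whether the device outputs raw or adjusted values. A full protocol may give the nurses' method. This stands, and it limits what can be claimed. Three stronger readings are tempting and should not be drawn.

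- A reader might infer that nearly every patient will be an event at the low cut-off. That depends on an offset. Without one, the patch figure falls to 64% at a body mean of 37.5°C, and the nurse figure to about 20%.
- A reader might infer that the patch will miss fever. Under-detection is likely with an offset of 0.5°C or more, but it is not certain. With an assumed skin mean of 36°C, SD 0.7°C, half the variance between patients and 864 independent readings, about 21% of patients would still reach 38°C. Serial correlation would lower that; a skin mean of 35°C gives 0.4%.
- A reader might infer that temperature lies outside the device's approvals. Limitations discloses that "only blood pressure measurement passed validation testing for accuracy" and then relies on FDA and European approval. The device section describes the FDA clearance as "510K clearance for measurement of arterial pressure, oxygenation and HR", which does not include temperature, but it does not state the scope of the CE approval. Only the FDA part of that reliance has a gap.

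It can also be said that Bland-Altman analysis for repeated measurements is already planned, with an open list of parameters, and that artefact rules exist. Bland-Altman could reveal an offset but would not change who counts as an event, and a correct skin reading is not an artefact. Finally, thresholds may be reported one by one, which would confine saturation to the low item.

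**Conclusion.** The point holds as a flaw in a secondary outcome. The text itself fixes one site-free list of cut-offs, applies it to a skin sensor and to ward temperature, and tests the two against each other. That comparison cannot separate better detection from a different measurement site.

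The size is conditional. If nurses measure somewhere other than chest skin and skin reads at least 0.5°C lower, 97-100% of patients are patch-positive at the low cut-off, kappa approaches 0 and McNemar tends to favour the patch. The high cut-offs would then probably be under-detected. With no offset, patch positivity is 64-99%. Nurse positivity at the low cut-off runs from about 20% to 83% for assumed means of 37.5 down to 36.9°C, so whether it marks an abnormality needs checking; the document does not settle it. The main outcome, mean arterial pressure below 60 mmHg, and N = 114 are unaffected.

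**What to change.** - Take sensor temperature out of the two-by-two, kappa and McNemar analysis. Report it descriptively and by the planned repeated-measures Bland-Altman analysis, naming temperature among its parameters.
- Report the Table 1 temperature events from nurse data, and state the nurses' measurement site and method.
- Check the 36.8°C cut-off against the full protocol and reconcile it with the label of abnormality. This review does not say what the value should be.
- In Limitations, note that the 510(k) clearance as described does not list temperature.

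The cost is wording in Table 1, Statistics and Limitations, and notification of the ethics committee under the plan's own rule for modifications. No new data are needed. The downside is the loss of one nominal sensor-versus-nurse comparison.
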